#### Clinical assessment

To evaluate elbow flexion strength, the Elbow Strength Index (ESI) will be calculated. The ESI is calculated by dividing elbow flexor power with the lower arm in full supination by that of the contralateral upper extremity using a dynamometer (www.idorth.com) Innovative Design Distributors, London, UK [10, 24].

#### Imaging

Postoperative MRI, after 1 year is used to assess location of the proximal biceps tendon with regard to the bicipital groove. Absence of the biceps tendon in the bicipital groove confirms a successfully performed LHB tenotomy. Absence of the biceps tendon in the bicipital groove confirms failed LHB tenodesis. The rotator cuff is classified as fully healed, partially healed or recurrent rupture. Also the quality of the rotator cuff is scored according to Patte and Goutallier [25, 26].

#### Duration of surgery and complications

Surgeons will report the start and end times of their tenotomy and tenodesis procedures, so the duration of surgery can be calculated. In addition, all complications reported by patients up to 1 year follow up will be registered.

### Sample size

Sample size calculations are based on the Constant score, to evaluate the primary hypothesis: LHB tenotomy does not lead to inferior functional results at 1 year postoperative than LHB tenodesis when performed in conjunction with an arthroscopic repair of a moderately sized supraspinatus/infraspinatus tear in patients 50 years or older.

In 2013 Kukkonen et al. [27] presented results on minimal important change in rotator cuff surgery. Based on these data we performed a calculation of the sample size. Anticipating a difference of less than ten points on the Constant Score and a standard deviation of 16 points in both groups, we calculated the sample size using Study size 2.0 Software. To detect non-inferiority using a one-sided, two-sample t-test with an 80 % power and a significance level (alpha) of 0.025, group sample sizes of 41 patients are needed. Anticipating a dropout rate of 20 %, a total of 98 patients will be included. METC approval Nov 18, 2014 (NL 37898.100.11).

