**Methods:**

Patients older than 50 years with a supraspinatus and/or infraspinatus tendon rupture sized smaller than 3 cm, who are encountered with LHB pathology, will be randomized to either LHB tenotomy or LHB tenodesis. Clinical and patient-reported data will be collected pre-operatively, 6 weeks, 3 months and 1 year after surgery.

Primary outcome is overall shoulder function evaluated with the Constant score at 1 year after surgery. As additional measures of shoulder function, two patient reported outcomes (the Dutch Oxford Shoulder Test and the Disabilities of the Arm Shoulder and Hand questionnaire) will be assessed. Other evaluations include cosmetic appearance evaluated by the “Popeye” deformity, elbow flexion strength, arm cramping pain, MRI-based location of the biceps tendon, quality of life, and duration of surgery. To detect non-inferiority with a one-sided, two-sample t-test with 80 % power and a significance level (alpha) of 0.025, the required sample size is 98 patients.

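### With the plan's own 20% dropout, 98 patients leave about 39 per group rather than the 41 it requires, so power is about 78% rather than 80% (minor)

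*Protocol article*

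**What the plan says.** The Sample size section of the protocol article bases the calculation on the Constant score at 1 year. It gives these inputs: "Anticipating a difference of less than ten points on the Constant Score", "a standard deviation of 16 points in both groups", and "a one-sided, two-sample t-test with an 80 % power and a significance level (alpha) of 0.025". From these it concludes that "group sample sizes of 41 patients are needed". The next sentence allows for 20% dropout and says that "a total of 98 patients will be included". The Trial design section sets 1:1 allocation, so the evaluable total required is 82.

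The Methods paragraph of the abstract gives the same alpha, power and test and states that "the required sample size is 98 patients", without mentioning dropout.

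**The concern.** A dropout rate is ordinarily a proportion of the patients included. On that reading, the number included multiplied by 0.8 should return at least 82. For 98 it does not, so the required group size, the dropout rate and the total cannot all hold together.

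The stake is the power of the primary comparison. The Statistical analysis section specifies an independent samples t-test on 1-year Constant scores, which uses only patients with an observed score. If dropout runs at the anticipated rate, the trial has slightly less power than stated, and a non-inferiority trial short of power is more likely to end inconclusively.

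**Working it through.** **Inputs (Sample size section unless noted).** Margin 10 points, reading the anticipated limit on the difference as the margin; SD 16 in each group; one-sided alpha 0.025; power 80%; dropout 20%; total 98; 1:1 allocation (Trial design section). One input is not stated and is assumed: a true difference of zero.

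**Step 1: reproduce the plan's group size.** By the normal approximation,

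n per group = 2 × (1.96 + 0.8416)² × 16² / 10² = 40.2, rounded up to 41.

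This matches the plan, which supports both the reading of 10 as the margin and the assumed zero difference. The evaluable total is 2 × 41 = 82.

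**Step 2: where 98 may come from.**
- Multiplying: 82 × 1.2 = 98.4 (per group 41 × 1.2 = 49.2, so 49 and a total of 98). This agrees with the stated total after rounding down.
- Dividing: 82 / (1 − 0.20) = 102.5, so 103, or 52 per group and 104 in total. This does not agree with 98.

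The gap is 103 − 98 = 5 patients, or 104 − 98 = 6 with equal groups.

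**Step 3: what 98 delivers.**
- 98 × 0.8 = 78.4 evaluable, about 39 per group.
- 98 keeps 82 evaluable only if dropout is at most 1 − 82/98 = 16.3%, that is 16 patients lost.

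**Step 4: power.** With noncentrality 10 / (16 × √(2/n)):

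| Evaluable per group | t-test (noncentral t) | Normal approximation |
|---|---|---|
| 41 | 79.8% | 80.8% |
| 40 | 78.8% | 79.8% |
| 39 | 77.8% | 78.8% |

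Splitting the survivors 39 and 40 gives 78.3% by the t-test. Averaging t-test power over random 20% dropout in each arm of 49 again gives 77.8%.

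**The case against.** The strongest objection concerns size. About two evaluable patients per group are lost, and about 2 points of power. The assumed SD matters more: at 39 per group, an SD of 15.5 would give 80.3% power and an SD of 17 would give 72.7%. Alpha, the margin and the validity of the primary test are untouched. All of this stands, and it is why the point is minor.

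Four stronger readings are tempting, but the article does not support them.
- *That the whole distance from 77.8% to 80% comes from the dropout step.* By the same t-test, 41 per group gives 79.8%, because 41 is what the normal approximation yields. The dropout step accounts for 79.8 − 77.8 = 2.0 points.
- *That the authors are known to have multiplied by 1.2.* The article does not print the step. That origin is an inference. The mismatch does not depend on it, since 20% loss from 98 cannot leave 82 however 98 was reached.
- *That the abstract contains a separate error.* An abstract condenses, and the body gives both the 41 and the dropout allowance. Read alone, the abstract attaches 80% power to 98 patients, whereas 49 evaluable per group would give about 86%. That calls for a clarification and is not a second finding.
- *That the trial is seriously underpowered.* Power of about 78% under the plan's own assumptions does not bear that out.

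It could also be said that condensation excuses the mismatch. It does not: every figure needed for the check is printed, and no other section reconciles them.

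**Conclusion.** The point holds as a minor arithmetic inconsistency in the Sample size section. At the stated 20% dropout, 98 patients yield about 78 evaluable, about 39 per group, against the 82 (41 per group) that the plan requires. Power is then about 78% by the named t-test, or 78.8% by the normal approximation, rather than 80%. The shortfall in patients to include is 5, or 6 for equal groups.

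The mismatch in numbers rests only on dropout being a share of those included. The power figures rest also on 10 points being the margin, SD 16, and a true difference of zero, which the article does not state but which reproduces its 41.

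**What to change.** Keep 98 and correct the statement. In the Sample size section, say that with 20% dropout about 39 patients per group remain and power is about 78%; or say that 98 patients keep 82 evaluable only if dropout is at most 16%. State there that a true difference of zero was assumed. For consistency, the abstract should give 98 as the number randomised, including the dropout allowance, with 82 evaluable patients as the number behind the power statement.

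This costs a few words, a slightly less favourable power figure and no extra patients. If the sponsor prefers to keep both 41 per group and 20% dropout as written, the total becomes 103, or 104 for equal groups, at a cost of 5 to 6 more patients.

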### Statistical analysis

Statistical analyses will be done using the Statistical Package for the Social Sciences (SPSS Chicago, Illinois, USA). Analyses will be performed according to the intention to treat principle. To test our main hypothesis that LHB tenodesis and tenotomy result in similar functional outcome at 1 year follow up, Constant scores will be compared between groups using an independent samples t-test. In the unlikely event that a baseline difference is observed between groups, the change in Constant score from baseline to 1 year post-surgery will be used for analysis. Given the non-inferiority design, a one-sided *P*-value <0.025 will be considered statistically significant. Statistical uncertainties will be quantified using 95 % two-sided confidence intervals.

To further compare recovery after the two surgical interventions, longitudinal data analysis (mixed model or generalized estimating equations (GEE)) [28] will be used. In the primary model, the Constant score will be included as the dependent variable, and treatment allocation (between subjects) and time (within subjects) will be included as the key independent variables. Other variables that may affect outcome (e.g. age, center of inclusion) will be included as covariates. The interaction between group and time will be assessed to evaluate whether the two treatment groups differed in change over time. The secondary outcome variables (e.g. shoulder function on the DASH and OSS, quality of life on the EQ5D, pain on the VAS, Elbow strength, MRI findings, and cosmetic appearance) will be analyzed in using similar models. For all longitudinal data analysis analyses, a two-tailed value of *p* < 0.05 is considered statistically significant.

To evaluate the relation between patient-reported and clinical measures of function, we will calculate correlation coefficients for continuous outcome measures (e.g. DASH and OSS questionnaires versus Constant scores and elbow flexion strength). To assess agreement between the presence of a Popeye deformity (y/n) as reported by the patient, clinician, independent observers, and based on MRI, we will calculate Kappa coefficients.

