## Methods

### Trial design

A prospective patient blinded randomized controlled multicentre trial, with parallel groups will be performed at 11 hospitals in the Netherlands: Gelre Ziekenhuizen, Apeldoorn; St. Antonius Ziekenhuis, Utrecht; Amphia Ziekenhuis, Breda; Groene Hart Ziekenhuis, Gouda; Onze Lieve Vrouwe Gasthuis, Amsterdam; Medinova, Rotterdam; MC Slotervaart, Amsterdam; Delairessekliniek, Amsterdam; Reinier de Graaf Gasthuis, Delft; Spaarne Ziekenhuis, Hoofddorp; Canisius Wilhelmina Ziekenhuis Nijmegen. Inclusion will be competitive. The allocation ratio between the two interventions will be 1:1 and a non-inferiority design will be used.

This trial is registered at the Dutch Trial Registry on Jan 18, 2012, file number NTR3255, and at ClinicalTrials.gov on Jan 14, 2016, ID number NCT02655848.

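### Non-inferiority rests on a t-test that, as described, seems to use only patients with a 1-year Constant score; the planned mixed model would be the better primary analysis

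*Protocol article*

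**What the plan says.** All places are in the Methods of the protocol article.

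- **Design and hypothesis.** Trial design: "The allocation ratio between the two interventions will be 1:1 and a non-inferiority design will be used". Sample size states the hypothesis that "LHB tenotomy does not lead to inferior functional results at 1 year postoperative than LHB tenodesis".
- **Margin and size.** Sample size uses "Anticipating a difference of less than ten points on the Constant Score" and "a standard deviation of 16 points in both groups". It arrives at 41 per group and a total of 98: "Anticipating a dropout rate of 20"%. The ten points are not called a margin, but they serve as one.
- **Primary test.** Statistical analysis: "Analyses will be performed according to the intention to treat principle". The main hypothesis is tested by an independent-samples t-test of Constant scores, with one-sided P below 0.025. If the arms differ at baseline, change from baseline to 1 year is tested instead. No other analysis population is named.
- **Longitudinal model.** The next paragraph plans a mixed model or GEE to compare recovery further: "In the primary model, the Constant score will be included as the dependent variable". It is judged at two-tailed p below 0.05, with no margin attached.
- **Available scores.** Table 1 schedules the Constant score before surgery, at 3 months and at 1 year.

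**The concern.** A t-test on 1-year scores can use only patients who have such a score, or for whom one has been imputed, and the article mentions no imputation. The change-from-baseline fallback needs a 1-year score too. If a fifth of patients are lost, the analysis labelled intention to treat is then in effect one of completers, and the scores already collected from lost patients are set aside. That is unbiased only if the losses are unrelated to outcome, or related to it to the same extent in both arms.

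The model that would use the earlier scores cannot support the claim as planned. It has no margin, and a non-significant two-sided result is not evidence of non-inferiority. Its GEE alternative, in standard unweighted form, needs data missing completely at random, so it gives up much of the advantage.

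A second, smaller point is that intention to treat alone is not conservative for non-inferiority. Patients who receive the other procedure pull the arms together, and the article names no supportive analysis that would show this.

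At stake is the trial's single main conclusion.

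**Working it through.** **Inputs from Sample size and Statistical analysis:** margin 10 points, SD 16, one-sided alpha 0.025, power 80%, 41 per group, 20% dropout, 98 in total. **Assumptions, not in the article:** the score gap between lost patients and completers, and the cross-over rates.

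**1. The plan's own figure.** With a true difference of 0, n per group = 2 × [16 × (1.960 + 0.842) / 10]² = 40.2, rounded up to 41. The stated figure reproduces.

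**2. What the dropout allowance implies.** 41 × 2 = 82, and 82 × 1.2 = 98.4, which matches the stated 98. Enlarging the sample in this way makes sense only if lost patients add nothing to the test. After 20% loss, 98 × 0.8 = 78.4 remain, about 39 per group. (Dividing by 0.8 instead would give 103.) Power at 39 per group is 77.8% by the noncentral t, so the loss of power is small. The issue is bias.

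**3. Standard error.** 16 × √(2/39) = 3.62 points.

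**4. Dropout that favours tenotomy.** Suppose the true deficit equals the margin, 20% of the tenotomy arm is lost, the lost patients would have scored k points below that arm's completers, and tenodesis losses are unrelated to outcome. The expected observed deficit is 10 − 0.2k. The false non-inferiority rate is 1 − Φ(1.960 − 0.2k/3.62), by normal approximation.

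| k (points) | Observed deficit | False non-inferiority |
|---|---|---|
| 0 | 10.0 | 2.5% |
| 2.5 | 9.5 | 3.4% |
| 5 | 9.0 | 4.6% |
| 10 | 8.0 | 8.0% |

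The noncentral t gives 7.9% in the last row.

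**5. Other directions.** If lost patients fall below completers by the same amount in both arms, the bias cancels and the rate stays at 2.5%. If instead the lost tenodesis patients are the ones 10 points worse, the bias is 2 points against tenotomy. The false non-inferiority rate falls to 1 − Φ(1.960 + 2/3.62) = 0.6%. With truly equal procedures, power falls from Φ(10/3.62 − 1.960) = 79% to Φ(8/3.62 − 1.960) = 60%.

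**6. Cross-over.** If c is the sum of the cross-over fractions in the two arms, a true deficit of 10 shrinks to 10 × (1 − c). For c of 5%, 10% and 20% it becomes 9.5, 9.0 and 8.0, so the rates are again 3.4%, 4.6% and 8.0%. A c of 10% means 5% switching in each arm.

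**The case against.** - **The article does not say that lost patients are excluded.** A t-test can be run on imputed data, and missing-data rules usually sit in an analysis plan. This stands: a reader might take exclusion as stated, but it is inferred from the choice of test and the dropout allowance. What the article does fix is which analysis carries the non-inferiority criterion, and that analysis makes no stated use of the earlier scores.
- **The longitudinal model is already planned, and the article even calls it primary.** It could reveal a marked discrepancy with the t-test. But that label refers to the main model within the further comparison of recovery. It has no margin and is tested two-sided, so it does not replace the t-test.
- **Dropout bias has no fixed direction.** This stands, as step 5 shows. A reader might infer that the plan leans towards non-inferiority. Nothing in the article supports that: patients are blinded for 1 year and both arms follow the same rehabilitation.
- **Cross-over should be rare.** Randomisation takes place in the operating room after biceps pathology and tear size have been checked, and the surgeons are experienced in both procedures. This stands, and a total of 10% to 20% is unlikely.
- **A per-protocol set is commonly left to the analysis plan.** This stands, so its absence here is not an error in itself. Exclusions after randomisation can also bias either way, and requiring both analyses to agree is a debatable convention.
- **A mixed model is not a full cure.** It assumes data missing at random and corrects the scenario in step 4 only as far as earlier scores predict the missing one. This also stands, but it is a weaker assumption than complete-case analysis needs.

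**Conclusion.** The point holds in a limited form. The article attaches its non-inferiority criterion to a t-test that, read with the dropout allowance, appears to rest on patients with a 1-year score, while the better suited model is kept as a further analysis without a margin.

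Under the assumed one-sided scenarios the false non-inferiority rate is about 3% to 8% instead of 2.5%. With equal informative loss it is unchanged, and with the opposite pattern the bias works against tenotomy. These figures show sensitivity and do not predict what will happen. They rest on 39 evaluable patients per arm, SD 16, a 20% loss and the assumed gaps. The cross-over part is minor. The documents do not support the stronger conclusions that the plan is biased towards non-inferiority or that lacking a per-protocol analysis invalidates it.

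**What to change.** 1. **Primary analysis.** Take the 1-year between-group difference and its 95% confidence interval from the planned mixed model, not GEE. Fit it to all randomised patients with any Constant score (baseline, 3 months, 1 year), with visit as a categorical factor. Conclude non-inferiority if the interval for tenotomy minus tenodesis lies wholly above −10, and call the ten points the margin.
2. **Sensitivity analysis.** Keep the t-test on observed 1-year scores, judged against the same margin.
3. **Supportive analysis.** Report a per-protocol analysis against the same margin, in patients who were eligible at arthroscopy and had the allocated procedure. Do not exclude tenodesis failures found on MRI. The Imaging section says "Absence of the biceps tendon in the bicipital groove confirms failed LHB tenodesis", and that finding at 1 year is an outcome of treatment, not a protocol deviation. Do not make agreement of the two analyses a formal condition.

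**Cost.** A change of wording and a little more analysis work, with no new patients, visits or measurements. The downside is reliance on a missing-at-random model. Patients lost before 3 months add little to the 1-year comparison, because only their baseline score is available.

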## Discussion

With this multicentre, prospective patient blinded randomized level I study we will contribute to elucidating the controversy in the treatment of LHB tendon pathology in arthroscopic rotator cuff surgery. If our main outcome measure, the Constant score, is not lower in the group that underwent tenotomy, this increases the level of evidence to support previously reported findings that functional outcome is similar between treatments. Our thorough assessment of Popeye deformity (by the patient, the treating surgeon, and blinded assessors using digital pictures, complemented with MRI imaging) will reveal how this patient population values cosmetic appearance. While a Popeye deformity is more common after tenotomy, it is to date unknown to what extent this bothers patients older than 50 years.

A limitation of this study is that our comparison of costs is limited to the duration of surgery, without taking into account any other financial aspects. With regard to surgical material, no differences are expected, as tenodesis can be performed with the same anchor that is already used for the rotator cuff repair. One could speculate that tenotomy may allow for earlier return to work or activities, but this potential advantage would be masked by our study design as both groups received the same post-operative rehabilitation instructions.

The results of this study will strengthen the evidence on potential risks and benefits associated with tenotomy and tenodesis. Insight in the differences between treatment effects is very important, as managing patient expectations is critical in current orthopaedic practice.

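### The primary analysis does not carry the ten-point limit the trial was sized on, so as written it specifies no non-inferiority test or decision rule

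*Protocol article*

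**What the plan says.** Trial design (Protocol article) fixes the framework: "The allocation ratio between the two interventions will be 1:1 and a non-inferiority design will be used". Sample size gives the hypothesis a direction, "LHB tenotomy does not lead to inferior functional results at 1 year postoperative than LHB tenodesis", and names the method: "To detect non-inferiority using a one-sided, two-sample t-test", with 80% power and alpha 0.025, giving 41 per group. The ten points enter only there, as an expectation: "Anticipating a difference of less than ten points on the Constant Score and a standard deviation of 16 points in both groups". They are not called a margin.

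Statistical analysis words the aim differently: "To test our main hypothesis that LHB tenodesis and tenotomy result in similar functional outcome". The method is that "Constant scores will be compared between groups using an independent samples t-test". A one-sided P below 0.025 counts as significant, with the non-inferiority design given as the reason. Two-sided 95% confidence intervals are planned to describe uncertainty. The section mentions no ten points, no null value and no direction, and it compares no interval limit with anything.

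Elsewhere the wording varies again. The end of the Background hypothesises that function will not differ between the treatments. The Discussion begins its interpretation with "If our main outcome measure, the Constant score, is not lower in the group that underwent tenotomy".

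**The concern.** An independent samples t-test, as normally run, has a null of zero difference. Non-inferiority needs a null placed at the margin. If the analysis section is followed with default settings, there are two ways to draw a conclusion, and neither is the one the trial was sized for:

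- **A significant one-sided result in favour of tenotomy.** This would show superiority, which the trial neither expects nor is powered for.
- **A non-significant result read as similarity.** This treats absence of evidence as evidence, and the 2.5% error rate no longer applies to the claim.

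This is more than detail left to another document. The article does state the test, the sidedness, the threshold and the interval, and what it states does not connect to its own sample size. The two readings can also disagree on plausible data: the Background reports that pooled Constant scores tended to favour tenodesis (p = 0.07), so a modest observed deficit for tenotomy is a realistic result.

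**Working it through.** **Inputs** (Protocol article, Sample size): ten points, SD 16 in both groups, one-sided alpha 0.025, power 80%, 41 per group, 98 in total with 20% dropout. Completers at that dropout: 98 × 0.8 = 78.4, about 39 per arm.

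**1. Reproducing 41 per group.** With margin 10 and true difference 0, the normal approximation is

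n = 2 × (1.960 + 0.842)² × 16² / 10² = 2 × 7.85 × 2.56 ≈ 40.2, rounded up to 41.

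This matches. With the noncentral t distribution, power at 41 per arm is 79.8%, and at 39 per arm 77.8%. A two-sided 0.05 superiority calculation for a ten-point difference also gives 41, so the number is consistent with a ten-point margin but does not prove that one was meant.

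**2. Standard error and interval.** SE = 16 × √(2/n); half-width = t(0.975, 2n − 2) × SE.

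| n per arm | SE | Half-width of 95% CI |
|---|---|---|
| 41 | 3.53 | 7.03 |
| 39 | 3.62 | 7.22 |

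**3. Three readings of the primary test** (difference = tenotomy minus tenodesis).

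(a) *Margin-based.* Conclude non-inferiority if the lower 95% limit exceeds −10. The observed difference must exceed −10 + 7.03 = −2.97 (41 per arm) or −10 + 7.22 = −2.78 (39 per arm). The chance of this is 79.8% or 77.8% if the arms are equal, and 2.5% if tenotomy is truly 10 points worse.

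(b) *Zero null, significant in favour of tenotomy.* The chance is 2.5% if the arms are equal, by definition of the test level.

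(c) *Zero null, not significantly lower taken as similar.* The result passes if the observed difference exceeds −7.03 (41 per arm) or −7.22 (39 per arm). If tenotomy is truly 10 points worse, the noncentrality is 10/3.53 = 2.83 or 10/3.62 = 2.76, and the chance of passing is 20.2% or 22.2%.

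**4. Where (a) and (c) disagree.** Observed deficits for tenotomy between about 3.0 and 7.0 points (41 per arm), or about 2.8 and 7.2 points (39 per arm), would count as not significantly lower under (c) but would fail non-inferiority under (a).

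**The case against.** The best case for the protocol has four parts.

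- **No zero null is written.** The analysis section makes the test one-sided because of the non-inferiority design, and the sample size section describes the same kind of test, at the same alpha, as one that detects non-inferiority. A margin-shifted t-test may well be what was intended. This stands, and it makes the figures for readings (b) and (c) conditional.
- **The interval is already planned.** Comparing the lower limit of the two-sided 95% interval with −10 is exactly the one-sided 0.025 test. A reader might infer that the trial cannot establish non-inferiority; that goes too far, because the needed quantity will be available. What is missing is the sentence that commits to using it.
- **Ten points functions as a margin in the sample size section.** It comes from data on minimal important change and reproduces 41. That is fair, but the analysis section never takes it up.
- **The article is condensed, and its Discussion sets no rule.** A reader might treat the *not lower* sentence as a separate success criterion. It is loose interpretive wording and no more. Condensation explains absent detail; it does not explain an analysis section that gives the test and threshold but restates the hypothesis without a limit.

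It is also tempting to count the passing of smaller true deficits, such as 5 points, as false conclusions. They lie inside the ten-point limit, so a non-inferiority claim there would be true. Only the probability at 10 points is an error rate.

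**Conclusion.** The point holds as a defect of specification. The protocol's only primary conclusion is non-inferiority, and the section that defines the primary analysis contains no margin, null value, direction or rule for the interval, while its hypothesis wording invites a test against zero. On SD 16 and 41 or 39 analysed per arm, reading a non-significant zero-null result as similarity would accept a true ten-point deficit about 20% to 22% of the time in place of 2.5%. Observed deficits of roughly 3 to 7 points would change the trial's conclusion according to the reading chosen.

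These figures describe what follows from each literal reading. They do not predict what the investigators will do. Nothing in the document shows that a zero-null test was intended, and nothing commits to the margin-based one. Being able to compute the right comparison later is not the same as having fixed it in advance.

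**What to change.** 1. In Sample size, call 10 Constant points the non-inferiority margin instead of an anticipated difference.
2. In Statistical analysis, replace the similarity hypothesis with H0: tenotomy minus tenodesis ≤ −10 at 1 year. State that non-inferiority is concluded only if the lower limit of the planned two-sided 95% confidence interval exceeds −10, which is equivalent to a margin-shifted one-sided t-test at 0.025.
3. State which Constant scale carries the margin. Primary outcome says summed scores will be normalised for age and gender, while the ten points are not tied to raw or normalised scores. Say also that the same margin and rule apply if the analysis moves to change from baseline, which Statistical analysis allows.
4. Bring the wording in the Background (no difference), Statistical analysis (similar) and Discussion (not lower) into line with this rule.

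The cost is wording only. The 41 per group, the test family, the data collected and the planned interval all stay as they are.

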#### Rehabilitation

Because the patients are blinded to their treatment, they all follow the same postoperative rehabilitation instructions. In the first 6 weeks postoperatively, patients wear a sling and only passive range of motion exercises are allowed under guidance of a dedicated shoulder physiotherapist. After 6 weeks, active movement is started and expanded gradually. Patients are not allowed to lift any objects heavier than one kilogram during 3 months.

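### The longitudinal models name neither the pre-operative score as a covariate nor a treatment difference at any visit; on the most natural reading this loses power

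*Protocol article*

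**What the plan says.** The Statistical analysis section of the protocol article sets out two layers. The first is the primary comparison, a t-test of the Constant score at 1 year. The second is a longitudinal analysis by "mixed model or generalized estimating equations (GEE"), meant to compare recovery further. In that model the score is the dependent variable and "treatment allocation (between subjects) and time (within subjects) will be included as the key independent variables". Covariates are an open list with age and centre as examples. The text adds that "The interaction between group and time will be assessed to evaluate whether the two treatment groups differed in change over time". DASH, OSS, EQ-5D, pain and elbow strength are to be analysed with similar models, at two-sided p < 0.05.

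Table 1 lists a pre-operative value for all of these outcomes. DASH, OSS, pain and EQ-5D have four time points (pre-operative, 6 weeks, 3 months, 1 year). The Constant score and elbow strength have three, because neither is measured at 6 weeks.

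On missing data, the Sample size section says "Anticipating a dropout rate of 20" per cent.

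**The concern.** The pre-operative score precedes randomisation, so it carries no treatment effect, but it predicts the later scores. It is best used as a covariate, or with both arms held to a common pre-operative mean. The article names it as neither. It appears as a column of Table 1, and the interaction is described as a question of change over time. That suggests a model in which the pre-operative visit is one of the outcome visits.

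Two things then follow. A group effect averaged over visits includes a visit at which the expected difference is zero. The interaction compares changes from a freely estimated baseline, which ignores that randomisation makes the arms equal there in expectation.

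The secondary outcomes are where the proposed drawbacks of tenotomy, such as loss of elbow flexion strength, would show. The Background hypothesises no difference in functional outcome, so an insensitive analysis would tend to look like agreement with it. The open choice of method adds a smaller issue: ordinary GEE needs data missing completely at random, while a likelihood-based mixed model needs only missing at random.

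**Working it through.** **The plan's own figure.** The sample size is for the primary test only: "one-sided, two-sample t-test with an 80 % power", "a significance level (alpha) of 0.025", margin 10, SD 16. The normal formula gives 2 × 16² × (1.960 + 0.842)² / 10² = 40.2, so 41 per arm; the t-test power at 41 is 79.8%. The total reproduces as 82 × 1.2 = 98.4, stated as 98. No figure is given for the longitudinal models.

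**Inputs.** From the article: 98 patients, 1:1, 20% dropout, so 49 × 0.8 = 39.2, taken as n = 39 per arm; two-sided 0.05; visits from Table 1. Assumed, because the article gives no values: equal variances, compound symmetry with correlation ρ = 0.3, 0.5 or 0.7, complete data on the 39, no expected pre-operative difference, and a largest difference of 0.6 SD. Power is large-sample, from the noncentral chi-square.

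**Step 1: group effect averaged over visits, pre-operative visit included.** With a constant post-operative difference D:
- four visits: (0 + D + D + D)/4 = 0.75 D
- three visits: (0 + D + D)/3 = 0.67 D

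**Step 2: joint group-by-time interaction, pre-operative visit included.** With visit differences d₁…d_k in SD units, noncentrality is λ = (n/2) × Σ(d_j − d̄)² / (1 − ρ), on k − 1 df. Growing difference (0, 0, 0.3, 0.6): Σ(d_j − d̄)² = 0.45 − 0.9²/4 = 0.2475. At ρ = 0.3, λ = 19.5 × 0.2475 / 0.7 = 6.90 on 3 df, power 58.2%.

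**Step 3: baseline-adjusted joint test of the m = k − 1 post-operative differences.** Given the pre-operative score, their covariance is (2/n)(1 − ρ)(I + ρJ), where J is the matrix of ones. Hence λ = (n/2)/(1 − ρ) × [Σd² − ρ(Σd)²/(1 + mρ)], also on k − 1 df. Same pattern at ρ = 0.3: 27.857 × [0.45 − 0.3 × 0.81/1.9] = 27.857 × 0.3221 = 8.97, power 71.0%.

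| Difference by visit (SD) | Test | ρ 0.3 | ρ 0.5 | ρ 0.7 |
|---|---|---|---|---|
| 0, 0, 0.3, 0.6 | interaction | 58.2% | 74.5% | 93.5% |
| | adjusted joint | 71.0% | 81.3% | 95.2% |
| 0, 0.6, 0.6, 0.6 | interaction | 62.4% | 78.5% | 95.4% |
| | adjusted joint | 93.2% | 94.6% | 98.7% |
| 0, 0, 0, 0.6 | interaction | 62.4% | 78.5% | 95.4% |
| | adjusted joint | 68.0% | 81.3% | 96.0% |
| 0, 0.3, 0.6 (three visits) | interaction | 50.5% | 65.7% | 87.5% |
| | adjusted joint | 73.5% | 80.1% | 92.6% |

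An early difference that fades (0, 0.6, 0.3, 0) gives the first pair of rows again, because compound symmetry ignores visit order.

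**Step 4: adjusted contrast at 1 year alone.** λ = 19.5 × 0.36 / (1 − ρ²) gives 79.3%, 86.4% and 96.0% for a 0.6 SD difference at 1 year. For the fading pattern it has 5%, the false-positive rate.

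**Step 5: post-operative visits only, no pre-operative level.** A constant difference has Σ(d_j − d̄)² = 0 across those visits, so the interaction has 5% at any ρ. The averaged group effect is then undiluted.

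**The case against.** The strongest reply is that the article does not state the model calculated here. It does not say that the pre-operative score is an outcome visit, how time is coded, or that the interaction is a joint test without visit contrasts. The covariate list is open, and an article may leave such detail to the full plan. This stands as a limit on the claim: a reader might infer that the plan commits to these features, but they are inferences from Table 1 and the wording on change over time. It does not remove the point, because the article does fix a model form, and using the pre-operative value as a covariate is a better method on data already collected.

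Second, dilution affects only a visit-averaged group effect. It does not affect the interaction, the term that the text ties to its question. In a reference-coded model with the interaction, the group coefficient is the difference at the reference visit. This stands, so a reader should not infer that every secondary estimate is shrunk towards zero.

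Third, the stated aim is to compare recovery, and a 1-year contrast alone would miss an early difference that fades. This also stands. But the gain does not need a 1-year target: the adjusted joint test keeps the recovery question and has higher power in every pattern tried.

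Fourth, the fact that "patients wear a sling and only passive range of motion exercises are allowed" in the first 6 weeks might suggest that the 6-week visit wastes a degree of freedom for all outcomes. It cannot do so for elbow strength or the Constant score, which are not measured then.

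Fifth, the GEE point is conditional: a mixed model is also offered, and the 20% is a planning allowance with no stated mechanism.

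**Conclusion.** The point holds in a limited form. The article's longitudinal model names no adjustment for the pre-operative score and no treatment difference at a visit. With the pre-operative score as a level of time, a visit-averaged group effect is diluted to 0.75 or 0.67 of a constant difference. The undiluted joint interaction gives up 5.6 to 30.8 percentage points of power against an adjusted joint test at ρ = 0.3, and 0.6 to 5.1 points at ρ = 0.7, over the patterns tabulated. With post-operative visits only, the interaction cannot see a constant difference.

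These sizes rest on 39 per arm, compound symmetry, equal variances and a 0.6 SD difference. The documents give no correlation or secondary effect size. A reader might infer a general bias towards no difference on all continuous secondary outcomes. The documents do not support that: the loss depends on correlation and pattern, and is small when correlation is high. The primary t-test at 1 year is not affected.

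**What to change.** For each continuous longitudinal outcome, model the post-operative visits with the pre-operative value as a covariate, or keep all visits and constrain both arms to a common pre-operative mean. Include visit as a factor, group-by-visit and centre. Report the group difference with 95% CI at each post-operative visit, including 1 year. If recovery as a whole is the question, add a joint test of those differences. Name a likelihood-based mixed model in preference to ordinary GEE, given the anticipated dropout.

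The cost is a change of analysis wording; no new data are needed. The unadjusted group-by-time test becomes supportive.
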